### Statistical Analysis

The data will be analyzed by using SPSS version 20.0 (IBM Corporation). Descriptive statistics (means, SDs, and frequencies) will be used to present the characteristics of the participants, and inferential tests will be used to analyze the differences among the groups. Analyses will be performed based on intent-to-treat principles. The outcomes (Numeric Pain Rating Scale, Roland Morris Disability Questionnaire, Fear Avoidance Belief Questionnaire, Tampa Scale of Kinesiophobia, Short Form-36 Health Survey, Brunel Humor Scale, Beck Depression Inventory, Beck Anxiety Inventory, and Pittsburg Sleep Quality Index scores and the pressure threshold for pain) will be analyzed by using generalized estimation equations to compare the M-group, P-group, MP-group, and U-group at baseline, after 8 weeks, and at the 12- and 24-week follow-ups. The effects of groups, time, and group interactions with time (group×time) will be analyzed. The Bonferroni post hoc test will be used to identify the differences among the means of all variables. Missing data will be handled via multiple imputation [28]. The α established as the level of significance will be *P*<.05 (95%) for all hypothesis tests. The effect sizes will be checked by using the Hedges g test. The magnitudes of effect sizes will be interpreted as *trivial* (<0.2), *small* (0.2-0.6), *moderate* (0.6-1.2), *large* (1.2-2.0), *very large* (2.0-4.0), and *perfect* (>4.0) [29]. To represent the effect of the intervention, the delta (∆) of the analyzed variables (∆ = x ®postintervention − x ®preintervention) will be calculated.

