### Goal of the Study

The primary aim of our study is to analyze the effectiveness of a program that includes MCEs and pain education. The secondary aims are (1) to clarify the effects of the program on pain outcomes, including the subjective intensity of pain and the pressure pain threshold, and compare the MCEs group (M-group) and MCEs+pain education group (MP-group) to the pain education group (P-group) and usual care group (U-group), the P-group and MP-group to the M-group and U-group, and all 4 groups; (2) to clarify the effects of MCEs on physiologic and psychologic stress measurements and compare the U-group to the M-group, the U-group and P-group to the M-group and MP-group, and all 4 groups; and (3) to clarify the effects of the pain education intervention on physiologic and psychologic stress measurements and compare the U-group to the P-group and U-group and the M-group to the P-group and MP-group.

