## Methods

### Study Design

Our study will be a parallel-group randomized controlled superiority trial with 4 arms, as shown in Figure 1. The target sample size is 900 individuals with LBP, who will be randomized (1:1:1:1 allocation) via computer-generated randomization. The groups will receive their assigned intervention according to the following allocations: (1) M-group, (2) P-group, and (3) MP-group; the U-group will receive the usual care intervention. Individuals will be instructed to not perform any form of physical exercise during the intervention period. We will compare the three types of interventions to determine their relative superiority to usual care.

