### Study Procedures

#### Sample Size Calculation

Sampling will be probabilistic, and patients will be extracted from the LBP waiting list. The required sample size was calculated by assuming a mean difference of 1.5 and an SD of 2.4 [27]; the study requires a sample size of 225 per group, that is, 900 individuals in total.

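### Pain analysis: baseline is modelled as an outcome visit rather than adjusted for, pre-to-post change is labelled the intervention effect, and no primary contrast or Bonferroni family is fixed

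*Protocol article*

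**What the plan says.** All references are to the protocol article.

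- **Model.** Statistical Analysis applies GEE to every outcome "to compare the M-group, P-group, MP-group, and U-group at baseline, after 8 weeks, and at the 12- and 24-week follow-ups". The terms are group, time and their interaction. Baseline is one of the four levels of time, and no baseline covariate is named.
- **Effect measure.** The same section states: "To represent the effect of the intervention, the delta" will be calculated, defined as the post-intervention mean minus the pre-intervention mean. The formula has no control-arm term.
- **Multiplicity.** "The Bonferroni post hoc test will be used to identify the differences among the means of all variables". The set of comparisons over which the correction runs is not given. For alpha: "The α established as the level of significance will be *P*<.05 (95%) for all hypothesis tests".
- **Question.** Study Design says: "We will compare the three types of interventions to determine their relative superiority to usual care". The Objective in the Abstract and the Study Overview both point to 8 weeks. The primary outcome definition (pain on the Numerical Pain Rating Scale, NPRS) names no visit.
- **Aims.** Goal of the Study places pain under the secondary aims ("The secondary aims are (1) to clarify the effects of the program on pain outcomes") and lists several groupings of arms to compare, including all four.
- **Timing of baseline.** Data Collection puts the baseline survey after allocation. Random Allocation and Blinding puts an initial evaluation before it.

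**The concern.** The trial asks whether each of three programmes beats usual care on pain, with 8 weeks as the time of interest. The analysis text does not lead to one estimate that answers this.

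First, baseline NPRS is collected but used only as another response. A comparison of week-8 means then ignores it, and the group-by-time contrast is a difference in change. Both are usually less precise than a comparison adjusted for baseline.

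Second, a pre-to-post change within an arm is not a treatment effect. Entry requires pain of at least 3 on movement, so some fall is expected without treatment. Usual care here is itself an 8-week, 16-visit exercise programme, so that arm should show a delta too. Read as labelled, all four arms could seem to have an effect when none differs from another.

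Third, with no primary visit or contrast and no stated Bonferroni family, a reader cannot tell which result decides the trial or what error rate it carries.

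**Working it through.** **Inputs from the protocol.** Difference 1.5 and SD 2.4 (Sample Size Calculation); 225 per arm, four arms, 1:1:1:1; four time points; alpha 0.05, taken as two-sided.

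**Assumed, not in the protocol.** Baseline to week-8 correlation r of 0.3, 0.5 or 0.7; equal SD at each visit; complete data.

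**The plan's own figure.** The sample size is given as "The required sample size was calculated by assuming a mean difference of 1.5 and an SD of 2.4", with power unstated. n per arm = 2(z₁₋α/₂ + z_power)² × 2.4²/1.5².
- 80% power: 2 × 7.85 × 2.56 = 40.2, so 41.
- 90% power: 2 × 10.51 × 2.56 = 53.8, so 54.

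The stated 225 is not reproduced. That is a separate matter; 225 is taken as given below.

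**Precision of the week-8 difference between two arms.**
- Raw means: SE = 2.4 × √(2/225) = 0.226.
- Difference in change (group-by-time): variance × 2(1 − r).
- Baseline-adjusted: variance × (1 − r²).
- Adjusted relative to change: (1 − r²)/[2(1 − r)] = (1 + r)/2.

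| r | SE raw | SE change | SE adjusted | Variance cut vs change | Variance cut vs raw |
|---|---|---|---|---|---|
| 0.3 | 0.226 | 0.268 | 0.216 | 35% | 9% |
| 0.5 | 0.226 | 0.226 | 0.196 | 25% | 25% |
| 0.7 | 0.226 | 0.175 | 0.162 | 15% | 49% |

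At r = 0.5 the 95% CI half-width goes from 1.96 × 0.226 = 0.44 to 1.96 × 0.196 = 0.38.

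**Power for 1.5 points.** Raw means: 1.5/0.226 − 1.96 = 4.7 standard errors, power above 99.9%. The least precise case, change at r = 0.3, gives 1.5/0.268 − 1.96 = 3.6, still above 99.9%.

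**Regression to the mean in delta (illustration).** Suppose the entry score is the analysed baseline. The expected fall is (1 − r) × 2.4 × φ(a)/[1 − Φ(a)], with a = (3 − μ)/2.4. At r = 0.5 this is 0.66, 0.54, 0.42 and 0.33 points for assumed source means μ of 4, 4.5, 5 and 5.5. If screening pain is a different measure, correlated 0.7 with baseline and 0.35 to 0.5 with week 8 (assumed), the factor (1 − r) becomes 0.2 to 0.35 and the fall is 0.13 to 0.46. It is the same in every arm, so it cancels from a between-arm difference but not from a within-arm delta.

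**Familywise error for pain.** 20,000 simulated null trials; between-visit correlation 0.3/0.5/0.7.

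| Bonferroni family | Upper bound | Simulated |
|---|---|---|
| Six pairs within a visit, any of three follow-up visits counting | 3 × 5% = 15% | 11.3 / 10.8 / 9.5% |
| All 24 (six pairs × four visits) | 5% | 4.1 / 3.9 / 3.5% |
| Three week-8 contrasts with usual care | 5% | 4.3 / 4.5 / 4.4% |

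A second simulation of the first row at 0.5/0.7 gave 10.8/9.2%.

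**The case against.** The strongest defence is that nothing here is invalid. Baseline as a level of time with group-by-time gives an unbiased difference in change, a Bonferroni correction is planned, and its exact family is commonly left to a statistical analysis plan, which is not shown. Pain is named as primary, usual care as comparator and 8 weeks as the time of interest. With over 99.9% power for 1.5 points, the lost precision cannot change the outcome if that effect is real. The other pairs also answer real questions, since the article seeks the most efficient intervention.

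Much of this stands, and it rules out several stronger readings that a reader might infer:

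- *That error for pain is inflated.* The text does not say so. It depends on the family, and over all 24 comparisons error stays below 5%. Adding the pooled contrasts from Goal of the Study at an uncorrected 0.05 would raise it to 22-26%, but those are secondary aims and nothing says they escape correction.
- *That every pair is tested at every visit.* This is a natural reading, not a statement in the text.
- *That the treatment effect is diluted.* A constant 1.5 would average to 1.5 × 3/4 = 1.125 in a group main effect over four visits, but the article does not make that main effect the primary test.
- *That delta will be tested and claimed as efficacy.* It is only to be calculated, and the section also plans tests between groups. The fault is one of labelling and interpretation.

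The defence does not answer two things that the article itself fixes: the unadjusted use of baseline, and a control-free delta named as the effect of the intervention.

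**Conclusion.** The point holds in a limited form. The planned interaction contrast is valid but gives away precision: 35/25/15% of its variance at an assumed r of 0.3/0.5/0.7, or 9/25/49% if raw week-8 means are compared. At r = 0.5 this is a half-width of 0.44 instead of 0.38 points. The gain lies in interval width and in smaller effects than the one assumed, not in power for 1.5 points. Delta is mislabelled, because it does not estimate superiority to usual care.

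Control of familywise error at 5% for pain is not guaranteed, rather than shown to fail: about 9-11% under one plausible family and 3.5-4.1% under another. All figures assume 225 analysed per arm, SD 2.4 and the stated correlations. Adjustment also presupposes a baseline measured before allocation, on which the article contradicts itself.

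**What to change.** Amend Statistical Analysis as follows.

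1. Analyse NPRS by GEE on weeks 8, 12 and 24, with baseline NPRS as covariate plus group, visit and group-by-visit.
2. Name three primary tests: motor control exercises, pain education and the combination, each against usual care at week 8, with Bonferroni or Holm over those three at 0.05 overall.
3. Report baseline-adjusted between-arm differences with 95% CIs as the effect. Keep delta as description only and drop its label as the effect of the intervention.
4. Declare other pairs, later visits and all other outcomes secondary.
5. Reconcile Data Collection with Random Allocation and Blinding, so that the NPRS used as covariate is measured before allocation.

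The cost is wording, and the remaining comparisons become secondary. This assumes that the evaluation before allocation already records NPRS; if not, that measurement must move ahead of allocation. The change should be made before outcome data are seen.

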## Results

The trial was presented to the municipal authorities and its practical applications were discussed in August 2022. The researchers are being trained to apply the questionnaires and carry out the interventions. Patient recruitment will begin at the end of 2022 and results are expected to be achieved by August 2023.

## Discussion

### Study Overview

Some studies have identified the positive effects of using a biopsychosocial approach in interventions for patients with chronic pain [9]. There is evidence that motor exercises reduce LBP through the activation of the deep lumbopelvic musculature [10].

In contrast to other randomized controlled trials, our study will investigate the effects of the association between motor exercises and pain education and compare them to the effects of an exclusively biopsychosocial approach.

The structure of our study reflects a scenario of actual clinical practice, and it will investigate the effects of the interventions on pain reduction after 8 weeks of intervention. A follow-up at 3 months after randomization will be performed to obtain information on pain and other clinical factors from the patients.

The results of our clinical trial study will give us information on the most efficient intervention strategies that will be implemented in a public health service within Brazil, which may be expanded to other physiotherapy centers and serve as a basis for planning health actions with the greatest impact on the population of people with LBP.

Future studies could explore the use of complementary modalities, such as mindful movements, among patients with chronic pain to identify the promotion of well-being.

### Study Implications

The structure of our study reflects a real scenario of actual clinical practice in a public health service. Its application may benefit many patients who have never been treated. The study proposal also offers a detailed exercise protocol and pain education approach that can serve as a reference for many professionals. Further, the identification of more appropriate intervention strategies for individuals with chronic LBP may result in changes in professional conduct and more treatment tools with a greater clinical impact.

### Conclusions

Our trial will provide preliminary data regarding the feasibility and safety of MCEs and pain education for patients with LBP. It will also provide preliminary outcome data that can be used to identify the most efficient intervention and the level of health care that should be implemented in public health services.

## Appendix

Multimedia Appendix 1 Pain Education Program.

## Abbreviations

LBP: low back pain
M-group: motor control exercises group
MCE: motor control exercise
MP-group: motor control exercises+pain education group
P-group: pain education group
SPIRIT: Standard Protocol Items: Recommendations for Randomized Trials
U-group: usual care group
